## Abstract

Stroke remains a leading cause of disability and mortality in Bangladesh, with limited data on risk stratification models tailored to the local population. Current prediction models inadequately capture the complex interplay of socioeconomic, environmental, and mental health factors prevalent in Bangladesh. This study protocol was designed to develop an artificial intelligence (AI)-based risk prediction model for stroke occurrence and poor long-term outcomes, specifically for the Bangladeshi population. The Foresighting Outcomes and Risk Evaluation with Computational Artificial Intelligence in Stroke Trials (FORECAST) study is an ambispective case-control study that will enroll 4,000 participants (2,000 stroke cases and 2,000 controls) from the National Institute of Neurosciences and Hospital, Bangladesh, between May 2022 and April 2026. We will develop ensemble machine learning models using comprehensive phenotypic data, including sociodemographic variables, comorbidities, anxiety/depression scores, and clinical parameters. The study will employ explainable AI techniques to enhance clinical interpretability and validation through k-fold cross-validation methods. The FORECAST study will establish the first AI-based stroke prediction model for Bangladesh, accounting for unique local risk factors, including rural-urban disparities and mental health comorbidities, with expected accuracy exceeding 90% based on recent advances in stroke prediction modeling. This study addresses critical gaps in stroke risk assessment for Bangladesh and similar low-middle-income countries by incorporating culturally relevant risk factors into advanced machine learning frameworks.

## Introduction

Stroke represents a significant global public health issue, and increasing incidence rates have substantially contributed to the national disease burden in Bangladesh [1]. The Global Burden of Disease Study 2019 identified stroke as a leading cause of death and disability-adjusted life years in South Asian populations, with Bangladesh experiencing particularly high stroke mortality rates, which may be attributed to an underdeveloped primary healthcare system and persistent financial constraints [2]. Current risk prediction models, predominantly developed in Western populations, inadequately capture the complex interplay of socioeconomic, environmental, and mental health factors prevalent in Bangladesh [3]. Recent advances in artificial intelligence (AI) have revolutionized stroke prediction capabilities, with ensemble learning methods achieving accuracies up to 99% and incorporating explainable AI techniques for enhanced clinical interpretability [4,5,6]. However, these sophisticated models remain largely untested in Bangladeshi populations, where unique risk factors, including high rural population density, limited healthcare access, and significant socioeconomic disparities, influence stroke outcomes [6]. Traditional risk assessment tools fail to account for these contextual factors, resulting in suboptimal predictions and missed opportunities for prevention [7].

Emerging evidence suggests that mental health comorbidities, particularly anxiety and depression, significantly influence stroke risk through complex pathophysiological mechanisms, including chronic inflammation, endothelial dysfunction, and behavioral factors [8,9]. Despite this growing recognition, the relationship between mental health and stroke remains underexplored in Bangladeshi populations, where cultural stigma and limited mental health resources create additional barriers to comprehensive care [10]. Furthermore, educational attainment and rural-urban residence patterns in Bangladesh create distinct risk profiles that require specialized modeling approaches to achieve optimal prediction accuracy [11].

The FORECAST (Foresighting Outcomes and Risk Evaluation with Computational Artificial Intelligence in Stroke Trials) study will address these critical knowledge gaps by developing and validating an AI-based risk prediction model specifically designed for Bangladeshi populations. By integrating advanced machine learning techniques with comprehensive phenotypic characterization, this study will establish a culturally appropriate and clinically actionable tool for stroke risk stratification in resource-limited settings.

## Materials and methods

The FORECAST study is an ongoing ambispective case-control study conducted at the National Institute of Neurosciences and Hospital (NINS&H), Bangladesh, in collaboration with the Institute of Cardiovascular Research, Royal Holloway, University of London, UK. This design allows for comprehensive characterization of stroke risk factors while maintaining feasibility within the Bangladeshi healthcare infrastructure between May 2022 and April 2026. The primary objective is to develop an AI-based risk prediction model that identifies independent predictors of stroke occurrence and poor long-term outcomes among Bangladeshi individuals. The study will also utilize explainable AI techniques to enhance the clinical interpretability of CT and MRI brain imaging findings, leveraging recent advances in stroke prediction modeling, with an anticipated accuracy rate exceeding 90%.

The study has received ethics approval from the institutional review boards of the National Institute of Neurosciences and Hospital (NINS&H), Dhaka, Bangladesh (reference number IRB/NINS/2025/492). Given the retrospective nature of case identification, a waiver of informed consent has been granted for historical data analysis, while prospective participants will provide written informed consent. Data anonymization follows international standards with secure storage and restricted access protocols. Written informed consent will also be obtained from a legal representative if the patient is unconscious or intubated.

Inclusion criteria encompass complete medical records availability and Bangladeshi residency for ≥5 years, while exclusion criteria include incomplete clinical data and previous stroke history for first-ever stroke analyses. Cases include adult patients (≥18 years) with acute ischemic or hemorrhagic stroke confirmed by a neuroimaging scan, either a CT/MRI scan, evaluated by two experts (neurologist and intervention radiologist). Stroke diagnosis will follow American Stroke Association (ASA) guidelines, confirmed by clinical evaluation and CT or MRI imaging. All patients with any form or severity of stroke, including mild, severe, prior, recurrent, critically ill, or intubated cases, will be included to reduce selection and reporting bias. Individuals with major comorbidities, such as other neurological disorders (e.g., brain tumors), severe systemic illnesses (e.g., cancer), secondary strokes due to other conditions (e.g., endocarditis, trauma), or those taking medications affecting stroke risk, will be excluded. Controls comprise age and sex-matched healthy adults without stroke history, recruited from hospital visitors and community health facilities, ensuring representative sampling across urban and rural populations. Controls will be 18 years or older, have no history of stroke, and must provide written informed consent. Hospitalized individuals are not eligible as controls. If spouse controls are unavailable, age- and sex-matched community volunteers will be recruited, with gender balance ensured through equal representation or sex stratification in analysis. The study will maintain equal proportions of males and females in both groups to address sex-related differences in stroke risk. Controls will be selected from the same geographic and socioeconomic backgrounds as cases to minimize population stratification and ensure comparability in environmental factors, lifestyle, and medication use.

The study will enroll 4,000 participants, comprising 2,000 stroke cases and 2,000 matched controls. Sample size calculations utilized established formulas for case-control studies with binary exposure, assuming 80% power, 5% significance level, and expected stroke prevalence of 35% in the exposed group versus 15% in the unexposed group [12,13]. This sample size ensures adequate power to detect clinically meaningful associations while accounting for potential data missingness and subgroup analyses. The formula for case-control studies with binary exposure:

n = [P₁(1-P₁) + P₀(1-P₀)] × (Zβ + Zα/2)² / (P₁ - P₀)²

where power (1-β): 80% (Zβ = 0.84); α: 5% (Zα/2 = 1.96), expected stroke prevalence in exposed group (P₁): 35%, expected stroke prevalence in unexposed group (P₀): 15%, and minimum detectable odds ratio: 2.0.

Calculation:

n = [0.35×0.65 + 0.15×0.85] × (0.84 + 1.96)² / (0.35 - 0.15)²

n = [0.2275 + 0.1275] × 7.84 / 0.04

n = 0.355 × 196 = 69.58 ≈ 1,740 per group

Accounting for 15% loss to follow-up and missing data: 1,740 × 1.15 = 2,000 per group

The total sample size will comprise 4,000 participants, divided into 2,000 cases and 2,000 controls.

Comprehensive data collection encompasses sociodemographic variables (age, sex, education level, rural-urban residence, occupation, income), clinical parameters (blood pressure, glucose levels, lipid profiles, body mass index), comorbidities (hypertension, diabetes mellitus, atrial fibrillation, coronary artery disease), lifestyle factors (smoking, alcohol consumption, physical activity), and mental health assessments using validated instruments including the Generalized Anxiety Disorder-7 (GAD-7) and Patient Health Questionnaire-9 (PHQ-9) scales [14,15]. Outcome measures include stroke occurrence (primary outcome) and long-term functional outcomes assessed using the Modified Rankin Scale at 90 days post-stroke (secondary outcome) [16]. Additional outcomes encompass stroke recurrence, mortality, and healthcare utilization patterns to provide comprehensive prognostic information.

The study will implement an ensemble machine learning approach integrating multiple algorithms to optimize prediction accuracy [17]. The modeling framework comprises four specialized modules: a sociodemographic module utilizing neural networks for processing education, rural-urban status, and socioeconomic factors; a clinical risk module employing random forest algorithms for traditional risk factors; a mental health module using gradient boosting to capture anxiety-depression patterns; and an outcome prediction module combining all inputs for final risk stratification [18,19].

Feature selection will employ correlation-based, mutual information-based, and wrapper-based methods to identify optimal predictor combinations while minimizing overfitting [20]. The study will address data imbalance issues through the Synthetic Minority Oversampling Technique (SMOTE) and other resampling methods to ensure robust model performance across all risk categories [21]. Model validation will utilize k-fold cross-validation (k = 10) with stratified sampling to ensure representative distribution across subgroups [22]. Performance evaluation will encompass accuracy, sensitivity, specificity, area under the receiver operating characteristic curve (AUC-ROC), and F1-score metrics, with target performance exceeding 90% accuracy based on recent advances in stroke prediction modeling [23,24].

To enhance clinical interpretability and trust, the study will integrate explainable AI techniques, including Shapley Additive Explanations (SHAP) and Local Interpretable Model-Agnostic Explanations (LIME) [25]. These methods will provide insights into feature importance, individual prediction explanations, and model decision-making processes, facilitating clinical adoption and regulatory approval (Figure 1).

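### Historical records can supply only cases, never controls, so data source is tied to case status and internal cross-validation cannot reveal the effect

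*Protocol article*

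**What the plan says.** All of the following is in Materials and methods of the protocol article unless another section is named.

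- **Design.** "The FORECAST study is an ongoing ambispective case-control study", running from May 2022 to April 2026.
- **Consent.** "Given the retrospective nature of case identification, a waiver of informed consent has been granted for historical data analysis". The retrospective element is thus attached to cases. A different rule applies to people enrolled going forward: "while prospective participants will provide written informed consent".
- **Controls.** They are "recruited from hospital visitors and community health facilities". The consent rule for them has no exception: "Controls will be 18 years or older, have no history of stroke, and must provide written informed consent". Inpatients are ruled out in a separate sentence: "Hospitalized individuals are not eligible as controls". No waiver route is given for them.
- **Eligibility.** Full medical records are required and incomplete clinical data lead to exclusion. The text does not limit either rule to one group, and does not say whether questionnaire scores count as clinical data.
- **Predictors.** These include "mental health assessments using validated instruments including the Generalized Anxiety Disorder-7 (GAD-7) and Patient Health Questionnaire-9 (PHQ-9) scales", together with income, physical activity and similar items. Anxiety and depression have their own gradient-boosting module. Historical and prospective participants are not distinguished.
- **Validation.** Stratified 10-fold cross-validation within the study sample, with a target above 90% accuracy.
- **Analysis** (Statistical analysis). Conditional logistic regression for the matched data and multiple imputation for missing values. Data source is not mentioned.
- **Limitations** (Discussion). Record quality, missing data and the lack of external validation are acknowledged in general terms, not as something that differs between cases and controls.

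The number of record-based cases is not given.

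**The concern.** A case-control comparison relies on exposure being ascertained in the same way in both groups. Here one group may mix records taken under a waiver with consented participants, while the other is wholly consented. A variable that is drawn from routine notes in many cases but collected at recruitment in controls will differ between the groups even if the underlying exposure does not. The same applies to anything that drifted over calendar time, if historical cases predate the controls.

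Two results are exposed. The first is the headline accuracy: a flexible classifier can use traces of the data source as if they were risk information. The second is the set of associations for variables obtained differently in the two groups. The mental-health associations would be among these if historical cases' scores were obtained by another route. SHAP and LIME would then attribute the artefact to the predictor that carries it.

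**Working it through.** **Step 1. Entry routes, from the stated consent and selection rules**

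| Route | Cases | Controls |
|---|---|---|
| Historical record, consent waived | Allowed | Closed: written consent required, inpatients barred |
| Prospective, written consent | Allowed | The only route |

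The asymmetry follows from the text. It does not depend on anything left out of the article.

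**Step 2. Do the stated safeguards remove it?**

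- *Matching and selection* cover age, sex, geography and socioeconomic background. They do not cover data source or calendar time.
- *The completeness rule* selects among historical cases. It does not make a recorded value equivalent to one obtained at recruitment.
- *Multiple imputation* fills gaps. It does not change how the observed values were obtained.
- *Ten-fold cross-validation* draws every fold from the same mixture, so a rule that exploits source performs as well in the held-out fold as in training.

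**Step 3. How large could the effect on accuracy be?**

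The plan gives no figure on this point to reproduce. Inputs from the article are 2,000 cases, 2,000 controls and the 90% target. The assumed input is x, the record-based share of cases, shown over a range because it is not stated.

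Take a rule that uses source alone, calling every record-based participant a case and everyone else a control. If record-based cases are fully recognisable:

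accuracy = (2000x + 2000) / 4000 = (1 + x) / 2

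| x | Calculation | Accuracy |
|---|---|---|
| 0.25 | (500 + 2000)/4000 | 62.5% |
| 0.50 | (1000 + 2000)/4000 | 75% |
| 0.80 | (1600 + 2000)/4000 | 90% |

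The AUC of this rule is the same, 0.5 + x/2. With an equal source mix in both groups, or with prospectively consented participants only, it falls to 0.50.

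**Step 4. Inflation on top of genuine discrimination**

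Assume a model with sensitivity and specificity both 0.75 among participants assessed alike, and suppose every historical case is also recognised:

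apparent accuracy = (2000x + 2000(1−x)·0.75 + 2000·0.75) / 4000

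- x = 0.50: (1000 + 750 + 1500)/4000 = 0.8125, about 81%
- x = 0.80: (1600 + 300 + 1500)/4000 = 0.85

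The second figure is below the 90% in Step 3 because this model misclassifies a quarter of the controls, whereas the source-only rule misclassifies none.

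**Step 5. Does missingness alone bias the odds ratio?**

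If a score is missing in some cases for a reason unrelated to its value, only the case sampling fraction changes, and the logistic slope is unaffected. A simulation with 2,000 cases, 2,000 controls, a true log odds ratio of 0.40 and 300 replicates deleted the score in a random 67% of cases. The mean estimate was 0.397, against 0.399 with full data. The standard deviation rose from 0.035 to 0.050. So precision is lost, with no material bias. Bias needs something further: a different measurement method, drift over time, or missingness that depends on the score.

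**The case against.** The strongest reply has four parts.

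*The key steps are inferences.* The article does not say that controls are assessed face to face, nor that patients under the waiver are never contacted. The records requirement is not confined to cases, so some control variables may also come from records. This stands. A reader might infer that all controls are interviewed and no historical case can be. The documents establish only the entry routes, so a difference in measurement method is probable rather than stated.

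*The accuracy figures describe a model nobody plans.* No section uses data source or a missingness flag as a predictor, imputation would fill the gaps, and the completeness rule might exclude cases without scores. This stands as a limit on size: (1+x)/2 is a ceiling for a source-only rule. It does not remove the mechanism, because recorded values can carry the mark of their source without any flag.

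*Some conclusions would go too far.* A reader might infer that every interview-based odds ratio is biased; Step 5 shows that purely missing scores need not cause bias. A reader might also take the 2025 in the ethics reference as the approval date, count 32 of 48 study months before it, set x = 32/48 ≈ 0.67 and expect about 83% accuracy from source alone. That needs approval at the very start of 2025, even accrual, every earlier case to be waiver-based, and full recognisability. The documents support none of these.

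*Analysis sets belong in the SAP, and the Discussion concedes data-quality limits.* The detail of a subset analysis may indeed sit in a document not shown. But the asymmetry is in the entry rules that the article does state. The Discussion also treats record problems as something that may lower accuracy. A difference by case status can raise it.

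**Conclusion.** The point holds as a design risk with a bounded but unknown size. It is established that historical data under the waiver can enter only the case group, and that no safeguard stated in the article makes source or calendar time comparable or would expose the difference. It is probable, not stated, that measurement method differs as well.

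Pooling as described can therefore give an inflated headline accuracy, and biased associations for variables measured differently in cases and controls. Where scores are only absent in historical cases, for reasons unrelated to their value, the harm to the odds ratio is lost precision.

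The source-only ceiling of 62.5%, 75% and 90% at x = 0.25, 0.50 and 0.80 rests on 1:1 group sizes and full recognisability. The documents do not support reading it as a prediction of what the study will report, or as showing that the 90% target will be met artificially. It shows that, depending on x, the target could be approached partly through data source without internal validation revealing it.

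**What to change.** 1. State the number of record-based and prospective cases, their calendar periods, and how each predictor is obtained by group and source.
2. Report discrimination, accuracy and calibration separately for record-based and prospective cases.
3. Base the GAD-7, PHQ-9 and other interview-type associations, and a prespecified version of the occurrence model, on prospectively consented cases and their controls, measured with the same instruments over the same period.
4. Use record-based cases only for variables recorded in the same way in both groups.
5. State that neither data source nor missingness may enter as a predictor. The plan does not propose this, but flexible learners can adopt it by default.

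These are changes to reporting and analysis wording and need no new recruitment. The cost is fewer cases for the interview-based predictors, hence wider intervals, and possibly a lower headline accuracy.

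### Eligibility rules select on the comorbidities the model is meant to use, and select controls, but not cases, on health and stroke history

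*Protocol article*

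**What the plan says.** All the relevant text is in the Protocol article, Materials and methods.

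- **Shared exclusions.** The rule opens with "Individuals with major comorbidities, such as other neurological disorders (e.g., brain tumors), severe systemic illnesses (e.g., cancer" and ends "or those taking medications affecting stroke risk, will be excluded". It is addressed to individuals in general, not to one group, and names no drug or drug class.
- **Cases.** "All patients with any form or severity of stroke, including mild, severe, prior, recurrent, critically ill, or intubated cases, will be included". Previous stroke is an exclusion only where the analysis concerns first-ever stroke.
- **Controls.** "Controls comprise age and sex-matched healthy adults without stroke history". The working criteria follow: "Controls will be 18 years or older, have no history of stroke, and must provide written informed consent", and "Hospitalized individuals are not eligible as controls". Controls are also to be chosen so as to "ensure comparability in environmental factors, lifestyle, and medication use".
- **Predictors.** Data collection covers "comorbidities (hypertension, diabetes mellitus, atrial fibrillation, coronary artery disease" among other variables, and a random forest module is built on the traditional risk factors.
- **Outcome and target.** The primary outcome is stroke occurrence, with no restriction to a first stroke. The accuracy target is above 90%, checked by 10-fold cross-validation.

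**The concern.** In a case-control study the controls should show how common each exposure is in the population that produced the cases. Here three rules act on the exposures themselves or on their close correlates.

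First, people with the four listed comorbidities are commonly treated with drugs that bear on stroke risk. If such people are excluded, mainly untreated or undiagnosed disease remains, and the model cannot learn what treated disease contributes. The same rule sits badly with admitting every recurrent stroke, since a recurrent case on preventive medication is covered by both the inclusion and the exclusion. It also sits badly with the aim of comparable medication use.

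Second, *healthy* is required of controls and has no counterpart for cases. If it means free of the four conditions, those conditions are stripped from one side of the comparison.

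Third, a previous stroke can occur only among cases, and the primary outcome is not confined to first strokes.

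At stake are the odds ratios for the main risk factors and the headline accuracy. Cross-validation would not expose the problem, because every fold comes from the same selected sample. SHAP and LIME could then present selection effects as risk factors. The limitations listed in the Discussion do not mention it.

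**Working it through.** The article states no figure on this point, so there is none to reproduce. The exposure shares below are assumptions for illustration, with hypertension as the example exposure. Excluded treated people are taken to come only from the exposed.

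**Formula.** Observed OR = [case odds × (1 − share of exposed cases excluded)] ÷ [control odds].

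**A. Healthy-control rule, with and without the medication rule on the case side**

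Assume 50% of cases are exposed (odds 0.50/0.50 = 1.0) and 25% of unselected adults (odds 0.25/0.75 = 0.333). Undistorted OR = 1.0/0.333 = 3.0. The control share in the table is the share left after all selection of controls.

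| Exposed cases excluded as treated | Case odds | Controls at 10% (odds 0.111) | Controls at 5% (odds 0.0526) |
|---|---|---|---|
| none | 1.0 | 9.0 | 19.0 |
| 50% | 0.5 | 4.5 | 9.5 |
| 70% | 0.3 | 2.7 | – |

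The last row shows that the two rules can offset each other: 2.7 is below the undistorted 3.0.

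**B. Medication rule alone, then with the healthy-control rule**

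Assume 60% of cases (odds 1.5) and 30% of controls (odds 0.429) are exposed, so OR = 3.5.

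- 50% of the exposed excluded in each group: (1.5 × 0.5)/(0.429 × 0.5) = 3.5. The OR is unchanged, but observed prevalence falls to 43% and 18%.
- 70% of exposed cases and 50% of exposed controls excluded: 0.45/0.214 = 2.1.
- 50% of exposed cases and 70% of exposed controls excluded: 0.75/0.129 = 5.8.
- 50% excluded in each group, and the healthy rule then removes half of the remaining exposed controls: 3.5/0.5 = 7.0. If it removes 90%: 3.5/0.1 = 35.

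So the medication rule alone can push the OR either way, whereas the healthy-control rule, if it bites, pushes it upward.

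**C. Prior stroke**

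Let r be the share of cases with a previous stroke; among controls it is zero by design. A perfect marker of prior stroke has sensitivity r and specificity 1, so its accuracy in a 1:1 sample is 0.5 + r/2. For assumed r of 10%, 20% and 30%, that is 55%, 60% and 65%. This is a ceiling for that marker alone: prior stroke is not a listed predictor and would act only through correlated variables such as comorbidities and mood scores.

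**The case against.** A fair defence has five parts.

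1. *Healthy may mean no more than stroke-free.* The working control criteria cover age, stroke history, consent and not being in hospital. None rules out hypertension, diabetes, atrial fibrillation or coronary disease, and the aim of comparable medication use does not suggest disease-free controls. This stands in part: the term is undefined, so the inflation is conditional. Both words are nevertheless in the text, and a recruiter may follow the stricter one.
2. *The medication exclusion applies to everyone.* This stands. It is not an asymmetry between groups. That asymmetry comes from *healthy*, no stroke history and not hospitalised on one side, against any form or severity of stroke on the other.
3. *First-ever analyses are foreseen.* This stands for those analyses only. The primary outcome carries no such limit.
4. *Broad inclusion narrowed by exclusions is normal.* This is true, and untreated people could still enter. The conflict is practical rather than strictly logical. The article also does not say how many recurrent cases, or how many intended users of the tool, take such drugs.
5. *A fuller protocol may settle the definitions.* It may. The rules as printed, however, point in different directions, which is more than condensed detail.

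A reader might infer that prior stroke separates the groups deterministically, or that odds ratios are certain to be inflated. The documents support neither. Prior stroke is not a listed predictor and would mark only some of the cases, and the net bias depends on treated shares and on a meaning of *healthy* that the article does not give.

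**Conclusion.** The point holds in conditional form. Followed as written, the rules select on the exposures being modelled, select controls on health and stroke history, and leave the primary comparison open to recurrent cases.

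The certain consequence of the medication rule, taken literally, is that treated people cannot be modelled; its effect on odds ratios has no fixed direction. Inflation of odds ratios and accuracy follows if *healthy* is taken to mean free of the listed conditions. On the assumptions in part A, an odds ratio of 3.0 could appear as anything from 2.7 to 19, depending on how the two rules combine. These values show sensitivity to the rules and do not estimate the actual bias, because the article gives no exposure or treatment shares. The contribution of prior stroke is limited and indirect.

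**What to change.** 1. Make first-ever stroke against stroke-free controls the primary stroke-occurrence analysis. Keep recurrent cases for the 90-day outcome model and for a separate analysis. State how matched sets that lose their case are handled, since conditional logistic regression is planned for the matched data.
2. Replace the healthy-adult wording by adults without prior stroke, whatever their other conditions. Apply the remaining non-stroke exclusions identically to cases and controls.
3. Reconcile the medication exclusion with the predictor list, with the inclusion of recurrent strokes and with the aim of comparable medication use, and say which medications it covers. Record medication use for every participant.
4. Flag each participant by the enrolment rule in force and report results by that flag.

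**Cost.** The changes need protocol wording, a dataset flag and one more recorded variable. The primary model will have fewer cases and some matched sets will be broken; the article does not give the recurrent share, so the loss cannot be sized here. Recruitment has run since May 2022, and people already turned away cannot be recovered. That should be stated as a limitation.

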## Results

Expected results and clinical impact

The FORECAST study will deliver the first AI-based stroke prediction model (Figure 2) specifically designed for Bangladeshi populations, with expected clinical and scientific impacts encompassing improved risk stratification leading to targeted prevention strategies, novel insights into mental health-stroke associations in South Asian populations, and cost-effective screening tools for resource-limited settings [27]. The model will provide personalized risk scores with confidence intervals, enabling clinicians to make evidence-based decisions regarding preventive interventions and resource allocation.

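### Spouses and hospital visitors are among the controls, so distress over a relative's illness may bias the anxiety and depression comparison, by an unknown amount and in an unknown net direction

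*Protocol article*

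**What the plan says.** Materials and methods defines the comparator: "Controls comprise age and sex-matched healthy adults without stroke history, recruited from hospital visitors and community health facilities". Inpatients are ruled out: "Hospitalized individuals are not eligible as controls". Later in the same paragraph comes "If spouse controls are unavailable, age- and sex-matched community volunteers will be recruited", which makes spouses the implied first choice and community volunteers the fallback. Cases have acute stroke and may be critically ill or intubated.

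Data collection, in the same section, includes "mental health assessments using validated instruments including the Generalized Anxiety Disorder-7 (GAD-7) and Patient Health Questionnaire-9 (PHQ-9) scales". The scores feed one of four modules, "a mental health module using gradient boosting to capture anxiety-depression patterns", and a final module combines all inputs. The primary outcome is stroke occurrence, that is, case against control.

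Mental health is a featured contribution. Under Results the study expects "novel insights into mental health-stroke associations in South Asian populations", and the Abstract, Discussion and Conclusions repeat the theme. Results also foresees community-based screening as a use of the work.

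The article does not say when the scales are given, what period they cover, or what share of controls will be spouses or visitors.

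**The concern.** A control group should show how common the exposure is among stroke-free people in the population that produced the cases. A spouse control is by definition the partner of someone who has had a stroke. A hospital visitor may well be there because a relative or friend is ill. Either route into the study could itself change the exposure being measured. If it does, the control scores partly reflect the way controls were found.

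The stated safeguards do not reach this. Controls are to resemble cases in geography, socioeconomic background, environment, lifestyle and medication use; current distress is not on that list. Ten-fold cross-validation cannot show the problem, because every fold carries the same mix of controls. SHAP and LIME would present any artefact as an explanation of risk. The Discussion concedes that external validation is limited but does not mention control source.

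At stake are the mental health and stroke associations, and the transfer of that part of the model to community screening, where most people are not dealing with a relative's acute illness. A larger sample does not reduce a bias of this kind.

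**Working it through.** The plan gives no figure on this point to reproduce. Its only computed figure is the sample size, which does not bear on it. What follows is an illustration; every input is assumed.

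**Inputs**
- True control prevalence of a positive anxiety or depression screen: p0 = 0.15 (assumed).
- True odds ratio: 2.0 (assumed; the plan names the same value as its minimum detectable odds ratio).
- f = share of controls who are spouses or visitors (not in the plan; varied).
- m = factor by which their prevalence is raised (not in the plan; varied).
- Case scores taken as unbiased (assumed, relaxed in the last step).

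**Case prevalence.** Control odds = 0.15/0.85 = 0.1765. Case odds = 2 × 0.1765 = 0.3529, so p1 = 0.3529/1.3529 = 0.261.

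**Observed odds ratio.** Observed control prevalence is pc = 0.15 × [1 + f(m − 1)], and the observed odds ratio is 0.3529 / [pc/(1 − pc)].

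With f = 0.5:
- m = 1.25: pc = 0.1688, odds 0.2030, odds ratio 1.74
- m = 1.5: pc = 0.1875, odds 0.2308, odds ratio 1.53
- m = 2: pc = 0.225, odds 0.2903, odds ratio 1.22

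Across control-source mixes:

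| f | m = 1.25 | m = 1.5 | m = 2 |
|---|---|---|---|
| 25% | 1.86 | 1.74 | 1.53 |
| 50% | 1.74 | 1.53 | 1.22 |
| 75% | 1.63 | 1.36 | 0.99 |
| 100% | 1.53 | 1.22 | 0.82 |

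With m = 1 there is no bias at any f.

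**When the association would reverse.** This needs pc > 0.261, that is f(m − 1) > 0.261/0.15 − 1 = 0.74. With half of controls affected, their prevalence would have to rise about 2.5-fold (1 + 0.74/0.5 = 2.48).

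**If case scores are raised as well.** Suppose cases are scored after onset and their prevalence also rises 1.5-fold: 1.5 × 0.261 = 0.391, odds 0.643.
- Against mixed controls (f = 0.5, m = 1.5): 0.643/0.2308 = 2.79.
- Against community controls only: 0.643/0.1765 = 3.64.

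Both exceed the true 2.0, and the community-only figure lies further from it. The control-side shift pulls the estimate down, but the net error can go either way, and correcting only the controls need not bring the estimate nearer the truth.

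**The case against.** Four objections deserve an answer.

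**Community sources are also named.** Controls come from community facilities and community volunteers too. The article does not say that visitors are relatives of cases or of acutely ill patients. Controls must also be sex-matched, which sits awkwardly with opposite-sex spouses, so the spouse share is unclear. This stands: a reader might infer that the comparator as a whole is contaminated, and the documents do not support that. The mechanism is most plausible for spouses.

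**Timing is not given.** The study is ambispective, and spouses of historically identified cases could be approached long after the acute illness. This also stands, and it makes raised scores a possibility rather than a fact.

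**The direction is not settled.** A reader might infer that the association is pulled to or past the null, or that the model learns distress as a marker of being stroke-free. That requires control scores to exceed case scores. In the illustration it happens only with a large affected share and a large rise, and only if case scores are unbiased. Post-onset scoring of cases works the other way. The objection defeats any claim about net direction. It does not remove the concern, because two unknown biases cannot be relied on to cancel.

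**Source coding and sensitivity analyses may sit in a fuller document.** That is fair for the form field taken alone. But the choice of spouses and visitors as controls, and the dedicated module for these scores, are stated in the article. The point rests on that combination.

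**Conclusion.** The point holds as a conditional design weakness. The plan prefers, or at least admits, controls whose anxiety and depression scores may be raised by a relative's illness, and it uses those scores for a featured association and a dedicated model module. Nothing stated protects the comparison.

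The size cannot be derived from the documents. With a true odds ratio of 2.0, 15% control prevalence, half of controls affected and unbiased case scores, the observed odds ratio would lie between 1.74 and 1.22 for a 1.25- to 2-fold rise. These figures show sensitivity to the source mix; they do not predict the result. The net direction is undetermined until the timing of the scales in cases is known. The concern is confined to the mental-health results and to the parts of the model that use these scores.

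**What to change.** - Record control source at enrolment: spouse, other visitor of an inpatient, or community volunteer. Recruitment runs to April 2026, and a source not recorded at entry may be hard to recover.
- Report the GAD-7 and PHQ-9 associations by control source.
- Pre-specify a sensitivity analysis restricted to community controls and adjusted for age and sex, alongside the matched analysis with all controls. Read both together with the timing of the scales in cases, since restricting the controls corrects one side only.
- For prediction, refit the whole model (mental health and combined modules) with spouse and visitor controls left out entirely, and refit it again without the mental health module. Do not simply blank these controls' scores: the scores would then be missing by design only among controls, so missingness itself would reveal control status and could inflate apparent accuracy.

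The cost is one extra form field and some additional model fits. The sensitivity analysis has fewer controls and broken matched sets, which is why it adjusts for age and sex instead of conditioning on the pair. The matched all-control analysis stays as planned.
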